## Abstract

**Background:**

After definitive chemoradiotherapy for non-metastatic nasopharyngeal carcinoma (NPC), more than 10% of patients will experience a local recurrence. Salvage treatments present significant challenges for locally recurrent NPC. Surgery, stereotactic ablative body radiotherapy, and brachytherapy have been used to treat locally recurrent NPC. However, only patients with small-volume tumors can benefit from these treatments. Re-irradiation with X-ray—based intensity-modulated radiotherapy (IMXT) has been more widely used for salvage treatment of locally recurrent NPC with a large tumor burden, but over-irradiation to the surrounding normal tissues has been shown to cause frequent and severe toxicities. Furthermore, locally recurrent NPC represents a clinical entity that is more radio-resistant than its primary counterpart. Due to the inherent physical advantages of heavy-particle therapy, precise dose delivery to the target volume(s), without exposing the surrounding organs at risk to extra doses, is highly feasible with carbon-ion radiotherapy (CIRT). In addition, CIRT is a high linear energy transfer (LET) radiation and provides an increased relative biological effectiveness compared with photon and proton radiotherapy. Our prior work showed that CIRT alone to 57.5 GyE (gray equivalent), at 2.5 GyE per daily fraction, was well tolerated in patients who were previously treated for NPC with a definitive dose of IMXT. The short-term response rates at 3–6 months were also acceptable. However, no patients were treated with concurrent chemotherapy. Whether the addition of concurrent chemotherapy to CIRT can benefit locally recurrent NPC patients over CIRT alone has never been addressed. It is possible that the benefits of high-LET CIRT may make radiosensitizing chemotherapy unnecessary. We therefore implemented a phase I/II clinical trial to address these questions and present our methodology and results.

**Methods and design:**

The maximal tolerated dose (MTD) of re-treatment using raster-scanning CIRT plus concurrent cisplatin will be determined in the phase I, dose-escalating stage of this study. CIRT dose escalation from 52.5 to 65 GyE (2.5 GyE × 21–26 fractions) will be delivered, with the primary endpoints being acute and subacute toxicities. Efficacy in terms of overall survival (OS) and local progression-free survival of patients after concurrent chemotherapy plus CIRT at the determined MTD will then be studied in the phase II stage of the trial. We hypothesize that CIRT plus chemotherapy can improve the 2-year OS rate from the historical 50% to at least 70%.

**Conclusions:**

Re-treatment of locally recurrent NPC using photon radiation techniques, including IMXT, provides moderate efficacy but causes potentially severe toxicities. Improved outcomes in terms of efficacy and toxicity profile are expected with CIRT plus chemotherapy. However, the MTD of CIRT used concurrently with cisplatin-based chemotherapy for locally recurrent NPC remains to be determined. In addition, whether the addition of chemotherapy to CIRT is needed remains unknown. These questions will be evaluated in the dose-escalating phase I and randomized phase II trials.

## Background

Despite substantial improvements in treatment outcomes for nasopharyngeal carcinoma (NPC) owing to new radiation technologies, such as X-ray—based intensity-modulated radiotherapy (IMXT), and concurrent chemoradiotherapy, local recurrence remains a common reason for treatment failure. Unfortunately, approximately 10%–15% of patients with non-metastatic disease will experience local recurrence after high-dose IMXT, with or without chemotherapy [1]. Re-treatment with definitive intent after high-dose IMXT poses a significant challenge to oncologists who specialize in head and neck cancer.

Several modalities have been used with some success in the re-treatment of local NPC when the initial treatments failed. For example, nasopharyngectomy, for a selected group of NPC patients with limited tumor volume in the post-nasal space, might achieve a long-term control rate of over 50% [2]. Re-irradiation using stereotactic radiosurgery or brachytherapy can also be used for recurrent foci with limited tumor volume [3, 4]. However, for more extensive local recurrences after high-dose radiation, IMXT is currently the treatment of choice in the endemic region. Several retrospective studies have addressed the long-term results of using IMXT for locally recurrent NPC; the documented 3- to 5-year overall survival (OS) rates for most patients who presented with locally advanced recurrent disease were usually less than 40% [5–7].

### Challenges in the re-treatment of locally recurrent NPC

Re-irradiation of locally recurrent NPC after a prior course of definitive radiation is challenging for many reasons. The high-dose volumes encompassed in the initial course of definitive radiotherapy for the primary disease consist of not only the gross tumor volume (GTV) but also the organs at risk (OARs), such as the pharyngeal mucosa, optic nerve/chiasm, temporal lobes of the brain, and brain stem, as necessitated for the coverage of subclinical disease. A substantial portion of the temporal lobes and most parts of the nasopharynx are often irradiated with a dose of 66–70 Gy, especially in patients with locally advanced recurrences. When the combined radiation dose of both initial radiotherapy and re-irradiation exceeds 100 Gy, the likelihood of radiation-induced adverse effects increases substantially (from 4% to 39%) [8]. Therefore, re-irradiation to a dose that exceeds 60 Gy may cause severe long-term adverse effects, including temporal lobe necrosis and soft-tissue ulceration and necrosis. Nasopharyngeal mucosal ulceration and necrosis is a potentially life-threatening condition. In addition to causing a significant reduction in quality of life, high-dose re-irradiation can cause death from necrosis, infection, or massive hemorrhage of the internal carotid artery, despite optimum clinical management.

Local recurrence of NPC after definitive radiotherapy with photons is most likely caused by radio-resistant NPC cells that survived the first course of radiation. Treatments might also fail locally due to the technical limitations of two-dimensional conventional radiotherapy or three-dimensional conformal radiotherapy, in which inadequate imaging, targeting, and delivery reproducibility may result in under-dosing of the primary disease and neck adenopathy. The prevailing use of IMXT, along with advanced imaging technology such as magnetic resonance imaging (MRI) and positron emission tomography/computed tomography (PET/CT), have significantly improved locoregional disease control over the years. Despite these advances, 10%–15% of patients who complete IMXT at 70 Gy still experience local treatment failure [1]. Therefore, having largely eliminated the technological limitations of treatment, it is reasonable to speculate that there are subgroups of cells within the gross disease that are more resistant to X-ray—based radiation and are enriched within recurrent tumors. Whether such features of radio-resistance are secondary to inherently radio-resistant clones, the presence of cancer stem cells, or hypo-oxygenation remains unknown. Regardless of the mechanisms, radio-resistance of the recurrent tumor confers a worse outcome after re-treatment using IMXT with doses similar to the initial radiotherapy (i.e., 60–70 Gy at standard fractionation). Thus, previous IMXT for primary NPC poses additional biologic challenges to re-treatment of local recurrence. This clinical scenario requires the targeting of a more radio-resistant disease while several critical OARs may have already been encompassed in the high-dose region. Nearly all patients reported in the literature so far were treated with two-dimensional conventional radiotherapy. As such, previous data may not be comparable to studies conducted in the IMXT era.

### Characteristics of particle radiotherapy in cancer treatment

Charged-particle therapy, such as proton therapy, helium therapy, and carbon-ion radiotherapy (CIRT), possess distinct physical characteristics that make it superior to photon therapy. These include a sharp lateral penumbra; minimal energy deposition within the beam’s entry path prior to the Bragg peak, which is defined by its steep dose deposition; and a sharp dose-deposition fall-off after the Bragg peak. Thus, beams exhibit both a precise and a finite range with respect to their dose delivery capability. The depth of the Bragg peak can be altered by altering the beam’s energy. These properties enable the sparing of surrounding normal tissues, which is crucial when irradiating the head and neck area, especially for patients who have received prior radiotherapy to this region. Several reports have shown improved dose distributions using particle therapy for primary or recurrent NPC, with acceptable efficacy and toxicity profiles [9–11].

In addition to its superior dosimetric properties, the heavy carbon ion is a high linear energy transfer (LET) modality. Furthermore, the relative biological effectiveness (RBE) of CIRT is substantially higher than that of photon- and even proton-based radiation. The value of RBE is 3–5 for carbon ion. The actual calculated value is dependent on both the tissue type and the biologic endpoint of RBE assessment. High-LET radiation inflicts more damage via direct DNA double-strand breaks, which are more difficult to repair [12]. Improved efficacy could be expected after the delivery of high-LET radiation, such as CIRT, especially in the treatment of photon-resistant cancer cells that have been selected for their ability to more efficiently repair DNA single-strand breaks. Per convention with CIRT (and other particle-based modalities), the differences in RBE and LET between CIRT and photon radiotherapy will be taken into account, and the CIRT doses will be reported in terms of gray equivalents (GyE), which refer to the biologic effective doses (BEDs) of photons.

Results from retrospective and prospective studies have shown improved outcomes after CIRT for several malignancies, including chordoma/chondrosarcoma of the skull base [13, 14], melanoma [15], and adenoid cystic carcinoma of the head and neck region [16]. These results also demonstrated the safety of CIRT to critical OARs such as the optical nerve/chiasm, brain, brainstem, and spinal cord. At the Heidelberg Ion-Beam Therapy Center in Germany and the National Institute of Radiological Sciences in Japan, CIRT is currently the routine treatment for patients with these conditions.

### Particle therapy for local recurrence in head and neck cancers

Particle therapy has also been used successfully in the re-treatment of local recurrences of the above-mentioned conditions of the head and neck, including locally recurrent NPC. In one study, 16 NPC patients who developed a local recurrence after conventional photon-based radiotherapy and were re-irradiated by proton radiation achieved an OS rate of 50% [11]. Those who were re-irradiated with 61 Gy or more achieved a local control rate of 60%; however, the local control rate was only 38% for those irradiated with a lower total dose (*P* = 0.17) [11]. The median cumulative dose of both the initial radiotherapy and re-irradiation was 133.5 Gy (range, 110–148 Gy). The 2 of 9 (22.2%) surviving patients who developed osteonecrosis and mucosal necrosis were successfully treated with surgical debridement and hyperbaric oxygen. With radiation doses of 60.0, 60.0, and 57.0 Gy to the optic chiasm, surface of the brainstem, and center of the brainstem, respectively, no patient experienced clinically detectable neurological dysfunction [11].

A series from the Heidelberg Ion-Beam Therapy Center included 18 patients with base-of-skull tumors who developed local recurrences after an initial course of radiotherapy and were re-irradiated with CIRT to a median dose of 51 GyE (range, 42–60 GyE) over 17 consecutive days (3 GyE per daily fraction) [17]. In this study, 3 of 18 patients received two courses of radiotherapy prior to the re-irradiation and received CIRT for their third course. Based on this calculation, the cumulative biological effective dose with an α/β ratio of 2 (BED2; usually for late-responding tissue) and cumulative biological effective dose with an α/β ratio of 9 (BED9; usually for tumor and early-responding tissue) were 127.5 and 68 GyE, respectively, using an α/β value of 2 for late toxicity of normal tissue. No patient developed grade 3 or 4 early or late toxicities.

### Concurrent chemotherapy with CIRT for locally recurrent NPC

Concurrent chemotherapy with IMXT is the current standard treatment for locally advanced NPC and has been studied against other chemotherapy scheduling [18, 19]. However, the addition of chemotherapy during IMXT for re-irradiation of locally recurrent NPC has never been studied in any prospective clinical trial. In the above-mentioned retrospective studies, some patients with recurrent NPC were treated with IMXT plus chemotherapy (either concurrent or adjuvant). However, multivariate analyses did not confirm that the addition of chemotherapy was a significant prognostic factor. The underlying mechanism of chemotherapy used with radiotherapy for recurrent NPC is not clear. However, in vitro studies have indicated the chemo-resistant characteristics of NPC stem cells [20]. It is reasonable to presume that locally recurrent NPC foci harbor chemo-resistant (and radio-resistant) cells that may reduce the efficacy of chemotherapy. In addition, the early onset of life-threatening adverse effects may mask the synergistic effects of combined chemoradiotherapy on disease control and survival.

The combination of CIRT with concurrent chemotherapy has never been studied prospectively for any malignancy. Given the superior physical and biological properties of CIRT and the potential benefits of concurrent chemotherapy, it is also reasonable to postulate that CIRT plus concurrent cisplatin-based chemotherapy may produce an optimal outcome in the treatment of locally recurrent NPC after high-dose IMXT. In this trial, we will first determine the maximal tolerated dose (MTD) of CIRT when used with concurrent cisplatin (weekly dose, 40 mg/m^2^) for the re-irradiation of locally recurrent NPC after IMXT. We will then evaluate the effectiveness of this strategy at the MTD.

### Selection of CIRT dose for re-irradiation in the phase I study

In the phase I part, we will use a Time-to-Event Continual Reassessment Method (TITE-CRM) design to determine, via a dose-escalation scheme, the MTD for re-irradiation using CIRT plus concurrent chemotherapy for the treatment of locally recurrent NPC [21, 22]. Patients will be monitored and evaluated for acute and subacute treatment-induced adverse effects, local control, local and distant progression-free survival, and OS.

Doses between 60 and 70 Gy (1.8/2.0 Gy per daily fraction) were commonly used for re-irradiation with IMXT for the treatment of locally recurrent NPC. Unfortunately, this dose range is associated with at least 35% of severe adverse effects (defined as grades 3–5 toxicities), including soft-tissue ulceration and hemorrhage, especially at higher doses [5, 7]. In a series of 239 patients treated with a mean dose of 70.04 Gy (range, 61.73–77.54 Gy) to the GTV, grades 3–5 re-irradiation-induced severe late toxicities occurred in approximately 52% of the patients and were the cause of death of almost 70% of the 120 patients who died [7]. More recently, in a study of salvage IMXT for the treatment of locally recurrent NPC after previous definitive IMXT, Kong et al. [23] reported a similar rate of severe toxicity (approximately 40%) after re-irradiation using IMXT. In addition, many patients developed two or more late toxicities after retreatment, and almost 70% of mucosal necrosis occurred within 6 months after re-treatment. Currently, a reduced dose range from 60 to 66 Gy at conventional fractionation (i.e., BED9 73–81 GyE) is commonly used for re-irradiation with IMXT for the treatment of locally recurrent NPC. However, long-term results after treatment at this dose level, especially for patients who recurred after receiving definitive IMXT for their primary treatment, have not been reported.

Two articles on re-irradiation using proton or heavy-particle therapy have reported clinically acceptable long-term toxicity outcomes. In these studies, a BED2 of approximately 120 GyE was delivered to the recurrent tumor. Doses of re-irradiation using proton and carbon ion exceeding or below 120 GyE conferred grade 3/4 late toxicity rates of approximately 22% and 0%, respectively [11, 17]. A total dose of 55 GyE (at 2.5 GyE per daily fraction) resulted in a BED2 of 124 GyE and a BED9 of 70 GyE. Since concurrent chemotherapy with CIRT may provide additive, if not synergistic, effects on efficacy as well as toxicity, 55 GyE at 2.5 GyE/day should serve as an acceptable starting dose/fraction schedule. In our previous phase I/II trial on CIRT alone for the treatment of locally recurrent NPC, we chose 57.5 GyE as the starting dose [24]. Owing to the potential additive toxicity of concurrent chemotherapy combined with CIRT, it will be prudent to set the starting dose of the phase I trial somewhat lower, at 55 GyE delivered at 2.5 GyE/day.

Because of the sharper penumbra offered by CIRT, we anticipate that the delivery of higher doses to the clinical targets—while potentially lowering the integral dose to, and high-dose volumes within, the non-targeted structures—will be more feasible compared with traditional photon-based radiotherapy. Because of these unique properties of CIRT, in addition to determining the straightforward MTD, toxicity will be associated with other unique dosimetric characteristics, such as dose-volume histogram parameters and gradient and conformality indices of the various BEDs within normal structures and tissues. This will provide supplemental three-dimensional and dynamic information to determine the tolerance of previously treated tissues to CIRT. Lastly, we will be able to determine the additive or synergistic effects of adding platinum-based chemotherapy to CIRT, as previous studies, with toxicity data, have consisted primarily of CIRT-alone regimens.

## Methods and design

As a single-center, single-arm phase I/II clinical trial, its purposes are to determine the MTD of re-irradiation using CIRT combined with concurrent cisplatin-based chemotherapy in the treatment of locally recurrent NPC and to evaluate the efficacy of this strategy at the determined MTD.

### Objectives

#### Phase I trial

The primary objective is to determine the MTD of CIRT combined with concurrent chemotherapy in the treatment of locally recurrent NPC, by observing the acute or subacute grade 4 or 5 toxicities [Common Terminology Criteria for Adverse Events (CTCAE) v. 4.03] that are possibly, probably, or definitively caused by the treatments [25]. The secondary objective is to evaluate the local progression-free survival and OS after re-irradiation using the combined treatment.

#### Phase II trial

The primary endpoint is 2-year OS after salvage CIRT with concurrent chemotherapy. The secondary endpoints are local control, disease-free survival, and long-term toxicity and safety.

### Trial design and schedule

#### Phase I trial: dose escalation to determine MTD

The purpose of the phase I trial is to determine the MTD of salvage raster-scanning CIRT with concurrent cisplatin-based chemotherapy for locally recurrent NPC. Patients who meet the inclusion criteria will be treated with chemotherapy and this dose-escalating CIRT scheme, and acute and subacute toxicity during the treatments and within 4 months after CIRT will be observed.

The study includes 6 increasing dose regimens starting at 52.5 GyE (2.5 GyE × 19 fractions) up to 65 GyE (2.5 GyE × 26 fractions) using the TITE-CRM design of phase I trials, with the starting dose/fraction at 55 GyE delivered daily in 22 fractions. The trial will be concluded at 65 GyE if the MTD is not reached, and 65 GyE/26 fractions will be the recommended dose/fractions for the phase II trial. The probability of dose limiting toxicity (pDLT) for each dose level is estimated based on published data for re-irradiation with CIRT to the head and neck area (Table 1).

**Table 1 Tab1:** Treatment schedule (CIRT plus concurrent chemotherapy) for dose escalation in patients with locally recurrent nasopharyngeal carcinoma (NPC)

Dose level	Dose and fractionation	Total dose (GyE)	pDLT (%)	BED2 (GyE)	BED9 (GyE)
1	2.5 GyE × 21 fractions	52.5	<5	118.1	67.1
*2*	*2.5 GyE* *×* *22 fractions (starting dose)*	*55*	*10*	*123.8*	*70.3*
3	2.5 GyE × 23 fractions	57.5	20	129.4	73.5
4	2.5 GyE × 24 fractions	60	30	135.0	76.7
5	2.5 GyE × 25 fractions	62.5	40	140.6	79.9
6	2.5 GyE × 26 fractions	65	50	146.3	83.1

The starting dose of the trial is at 2.5 GyE *×* 22 (in italics)

*CIRT* carbon-ion radiotherapy, *GyE* gray equivalent, *pDLT* probability of dose-limiting toxicities, *BED* biological effective dose, *BED2* cumulative BED with an α/β ratio of 2, *BED9* cumulative BED with an α/β ratio of 9

A maximum of 25 patients for the 6 dose levels (starting at 55 GyE) is projected for phase I trial (i.e., the dose-escalating stage of the trial). Based on our clinical load, we expect to recruit an average of 1 patient per week. We expect that the phase I trial will be completed in 24 months, since the first patient at each dose level will be followed up for 4 months before dose escalation.

#### Phase II trial: treatment at recommended dose to study efficacy

Once the MTD is determined in the phase I trial, this dose will be used as the recommended dose for the phase II trial. If MTD is not reached at 65 GyE, we will use 65 GyE as the recommended dose.

The primary endpoint of the phase II trial is OS after re-irradiation, at a median follow-up of 24 months. To evaluate the OS rate, all patients will be followed up for at least 12 months or until death. We estimate that 1 patient per week will be recruited to the trial, and a total of 40 patients (minus the number of patients treated at the recommended dose in the phase I trial) will be recruited over approximately 9 months. The phase II trial is expected to be completed in 24 months.

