#### Dose prescription for CIRT

Re-irradiation using intensity-modulated CIRT will be delivered using the IONTRIS raster scan system (Siemens Aktiengesellschaft, Munich, Germany). Six dose levels and the estimation of pDLT of each level are detailed in Table 1. A daily dose of 2.5 GyE will be delivered up to the total dose for all levels and be given concurrently with chemotherapy (see “Chemotherapy” above). After the MTD is determined or if the treatments to 65 GyE are safely delivered, the delivered dose (or 65 GyE) will be defined as recommended dose and used as the prescribed dose in the phase II stage of the study.

Ninety-five percent of the isodose line should cover the CTV for gross tumor (i.e., GTV plus 3–5 mm), and 90% of the dose line should cover the PTV for gross disease. The CTV for other subclinical disease, if applicable, will be irradiated to 90% of the assigned dose level.

Dose specification is based on BED, because the RBE of CIRT differs significantly from photon therapy. Therefore, the unit used for dose prescription is the iso-effective dose GyE daily for 5 fractions per week at 2 Gy per fraction.

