### Statistics (see footnote 1)

#### Phase I trial

The primary objective is to determine the CIRT dose when used with concurrent cisplatin-based chemotherapy, which is associated with a DLT in less than 25% of previously treated NPC patients with a local recurrence. DLT is defined as any grade 4 toxicity (CTCAE v. 4.03) that is possibly, probably, or definitely associated with CIRT that occurred within 6 months after completion of re-irradiation [24]. Treatment-induced adverse effects also include deterioration in Eastern Cooperative Oncology Group performance status to ≥3 that develops during the same follow-up period. The secondary objectives are OS and local progression-free survival. The MTD of CIRT for re-irradiation used with concurrent cisplatin-based chemotherapy will be determined at the end of phase I trial.

Dose levels of CIRT will be assigned based on the TITE-CRM algorithm [21]. During the trial, pDLT will be continually updated, using data from all enrolled patients and their updated outcomes obtained through follow-up visits. Patients with partial follow-up at a time of new enrollment (i.e., <4 months) will be weighted by the proportion of the follow-up time completed. Newly enrolled patients will be assigned to the dose that is estimated to have a pDLT closest to but not higher than 0.25.

Four patients will be entered to the starting dose level. Dose escalation is restricted to one level between any 2 patients. Prior to escalation, at least 1 patient must have completed the full course of treatment and the full observation period (6 months) at the previous dose level without a DLT. Six dose levels and their initial estimation of the pDLT are planned within the phase I trial (Table 1). The dose will be increased until DLT is observed or when 65 GyE is reached.

As described above, the phase I trial was designed to accrue up to 25 patients. We estimate that 4 patients will be accrued each month. Patients who complete 90% or more of the planned CIRT dose will be considered evaluable. Patients who complete 90% or more of the planned CIRT dose but become un-evaluable for 6 months will be counted as evaluable in the final analysis and weighted by the proportion of the observation period for which they were evaluable. Replacement of any accrued patient can only be considered if the patient did not complete therapy for reasons other than toxicity.

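### 65 GyE can become the phase II dose by default before any patient has completed the DLT window at it, although the plan requires a completed window to leave every lower level

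*Protocol article*

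**What the plan says.** Four places in the Protocol article bear on how the phase II dose is fixed.

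- Trial design, phase I: "The trial will be concluded at 65 GyE if the MTD is not reached", and 65 GyE is then the recommended dose. Table 1 in the same section gives initial pDLTs of <5, 10, 20, 30, 40 and 50% for levels 1 to 6, so 65 GyE stands at 50%. This section gives 4 months of follow-up for the first patient at each level before escalation.
- Trial design, phase II: "If MTD is not reached at 65 GyE, we will use 65 GyE as the recommended dose". The phase II total is 40, less however many phase I patients received the recommended dose.
- Dose prescription for CIRT: "After the MTD is determined or if the treatments to 65 GyE are safely delivered", the delivered dose (or 65 GyE) becomes the recommended dose.
- Statistics, phase I: the target is a DLT rate below 25%. "Four patients will be entered to the starting dose level". One condition must hold before a level is left: "at least 1 patient must have completed the full course of treatment and the full observation period (6 months) at the previous dose level"; that patient must also have been free of DLT. Also, "The dose will be increased until DLT is observed or when 65 GyE is reached". Assignment is model-based: "Newly enrolled patients will be assigned to the dose that is estimated to have a pDLT closest to but not higher than 0.25". The size is a maximum: "the phase I trial was designed to accrue up to 25 patients".

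**The concern.** The plan asks for more evidence to leave a level than to adopt the top one. Each lower level must have a patient who has finished treatment and the whole observation period without a DLT. For 65 GyE, the wording is satisfied when the level is reached or when treatment there has been delivered safely. Neither phrase carries a number of patients or an observation period, and delivery ends before the post-treatment part of the DLT window has run.

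This matters most at 65 GyE because the plan's own prior DLT rate there is twice its target. If the default takes effect early, up to 40 − 1 = 39 further patients could be treated at a level whose observed safety record is one partly followed patient. The background section on dose selection notes that, after photon re-irradiation, almost 70% of mucosal necrosis appeared within 6 months of re-treatment. That is another modality and not the DLT defined here, but it shows why the end of delivery is an early point at which to call a dose safe. A phase II dose above the toxicity target would also bring toxic deaths into the overall survival endpoint.

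**Working it through.** The article gives no derivation of the 25-patient maximum and no operating characteristics for phase I, so there is no figure of the plan's own to reproduce. The check has three steps.

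**1. Shortest path under the written rules.** Inputs: four patients entered at 55 GyE; one fully observed clean patient needed at each level before the next opens; escalation by one level at a time.

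- 55 GyE: 4; 57.5 GyE: 1; 60 GyE: 1; 62.5 GyE: 1. Total before 65 GyE opens: 4 + 1 + 1 + 1 = 7.
- The eighth patient is the first at 65 GyE. No sentence requires that patient, or any other at 65 GyE, to finish the observation period before the dose is adopted.

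So the minimum at the recommended dose is one treated and none fully observed.

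**2. How often that path is DLT-free if Table 1 is true.** Inputs: pDLT of 10, 20, 30, 40 and 50% for levels 2 to 6.

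- Reaches 65 GyE with no DLT: 0.9^4 × 0.8 × 0.7 × 0.6 = 0.6561 × 0.336 = 0.220.
- Also clears one patient at 65 GyE: 0.220 × 0.5 = 0.110.
- Even that cleared patient says little. The exact one-sided 95% upper limit for 0 DLTs in n patients is 1 − 0.05^(1/n), which for n = 1 is 0.95.

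**3. Whether the model cap of 0.25 would stop it.** The article states neither the working model nor the prior for the TITE-CRM, so these are assumptions: a one-parameter power model, pDLT_i = (skeleton_i)^exp(β), with the Table 1 values as skeleton and β ~ Normal(0, SD²). The data are 0 DLTs in 4, 1, 1 and 1 fully observed patients at levels 2 to 5. The level 1 skeleton value has no effect on the 65 GyE estimate because nobody is treated there. The estimate at 65 GyE, with the posterior mean of β plugged in, is:

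| Prior SD (assumed) | Estimated pDLT at 65 GyE | Against 0.25 |
|---|---|---|
| 0.5 | 0.353 | held below 65 GyE |
| 0.75 | 0.257 | held, narrowly |
| 1.16 | 0.134 | allowed |
| 1.34 | 0.094 | allowed |

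Taking the posterior mean of pDLT itself instead gives 0.356, 0.276, 0.191 and 0.167, with the same pattern. Whether the cap protects depends on a choice the article does not state.

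Two further inconsistencies affect the same decision. The observation before escalation is 4 months in the trial design section and 6 months in the Statistics section, so the completed window has no single length. And escalation until a DLT is observed is a different algorithm from assigning each patient to the level whose updated pDLT is closest to, but not above, 0.25.

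**The case against.** **A TITE-CRM pools information across levels and needs no per-level minimum to be valid.** This is correct. The absence of a fixed number at the selected dose would not by itself be a fault. The fault is narrower: the plan sets its own standard for leaving a level and its own 25% target, and its default rule for 65 GyE refers to neither.

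**The shortest path is a worst case.** With up to 25 patients over the five levels from 55 GyE, the average is five per level. At one patient per week, one treatment plus observation period at 55 GyE (22 fractions, 4.4 weeks, plus about 17.4 or 26.1 weeks) spans about 22 or 30 arrivals, so one patient per level would mean holding accrual. It is fair to call the path unlikely. But arrivals during that wait cannot go to a level that is not yet open, so fast accrual fills lower levels and does not secure patients at 65 GyE.

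**Other safeguards exist.** The review board looks at data semi-annually and can recommend termination, patients are evaluated weekly, and toxicity is a phase II secondary endpoint. These can limit harm once phase II is running. They do not set what must be known before it opens.

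**Stronger readings that the article does not support.** A reader might infer that 65 GyE could be adopted with nobody treated at it. The phase II design and dose prescription sections speak of the MTD not being reached at 65 GyE and of treatments to 65 GyE being delivered, which imply at least one patient there. A reader might also infer that the model could pick as MTD a level never given. The sentence usually cited for that, "Newly enrolled patients will be assigned to the dose that is estimated to have a pDLT closest to but not higher than 0.25", governs assignment of new patients; the article does not say how the final MTD is chosen, and a condensed article may leave that to the full protocol. Examples of such a selection also need a long run of DLT-free patients and an assumed prior.

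**Conclusion.** The point holds in this form: as written, the 65 GyE default can fix the phase II dose with one patient treated and none fully observed at it, although the same article requires a completed, DLT-free window to leave every lower level, targets a DLT rate below 25% and gives 65 GyE a prior pDLT of 50%. If Table 1's rates are true, the shortest path reaches 65 GyE without a DLT 22% of the time and also clears one patient there 11% of the time. These probabilities describe the shortest path if it is followed; they do not estimate how often the trial would end that way. The model cap is a partial safeguard, blocking the step at assumed prior SDs of 0.5 and 0.75 and allowing it at 1.16 and 1.34.

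This is a gap and inconsistency in the wording of a decision rule. It does not make the TITE-CRM design invalid, and it does not show that 65 GyE is the wrong dose. The photon re-irradiation figures in the background concern grade 3–5, largely late, toxicity and should not be read as expected DLT rates here.

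**What to change.** Reconcile the phase I design, phase II design, dose prescription and Statistics (phase I) sections so that adoption of the phase II dose, including the 65 GyE default, is expressed in terms of the plan's own completed DLT window and 25% target, in place of the level being reached or safely delivered. In the same revision, settle whether the window is 4 or 6 months, and whether escalation runs until a first DLT or follows the model. The sponsor should also state, and justify by operating characteristics under a stated prior, how many patients must be fully observed at the recommended dose before phase II opens. No number, dose or clinical rule is proposed here.

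The cost is protocol wording and a delay of about one observation window before phase II opens, or longer if the updated model moves the recommended level once that window has run. Patients treated at the recommended dose in phase I already count toward the 40, so observing them does not by itself enlarge the trial.
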